#### [contact] - [contact]

After verification of all selection criteria, an identification number shall be allocated to the patient and shall be maintained throu-ghout the trial. The identification number shall be faxed to the investigator. ***Investigator : Monitor :***

## 7.2 FIRST PHASE : Conformal 3 D radiotherapy with or without intensity modulation

23 fractions, 2Gy per session, will be delivered over a maximum of 42 days for a total dose of 46Gy (see appendix 1).

### 7.2.1 Patient positioning

Patient set-up is left free, as is the immobilization technique. However, set-up reproducibility within 5 mm must be verified weekly during treatment. The patient should be advised to have a rectal evacuation, if possible, before scanning and before each treatment session. A certain degree of bladder filling should be maintained (last miction 1 hour before CT-Scan and/or irradiation treatment followed by a glass of water).

### 7.2.2 Preparation for treatment – Placement of intra-prostatic markers (fiducials)

Intra-prostatic markers shall be implanted before examination by MRI or scanner. The choice of markers shall be left to the discretion of each participating center (gold seeds, …). These shall insure precise repositioning of the prostate (≤ 2 mm). They will also allow a precise fusion between the MRI and the dosimetric scanner.

This placement is recommended.

#### Fiducial markers

These are markers (gold seeds…) allowing the tracking of mobile lesions.

Treatment preparation includes the following steps :

- Consultation with the radiation oncologist
- Blood tests : PT, TCA, Platelets
- Placement of fiducial markers by a radiologist under ultrasound control (fiducial placement requirements and guidelines, appendix 7, see chapter 7.6 concomitant treatment)
- individualized immobilization system
- at least one week after fiducial placement: completion of planning scanner (recommendations appendix 7)
- dosimetry

### 7.2.3 Images acquisition

An MRI and scanner are done for the first treatment phase. CT-scan image acquisition is done in the treatment position, with the immobilization accessories. An intravenous injection of contrast agent must be given, in the absence of contraindication. Images must allow visualization of the anatomical structures, and also the markers implanted in the prostate. The bladder will be in intermediary state (neither full nor empty: last miction 1 hour before followed by a glass of water) and the rectum will be empty and non-distended.

CT-scan slices are up to 3 mm and obtained between the L5-S1 and the lesser trochanters.

After image transfer to the planning system, fusion with the prostatic MRI will be done, for a better definition of prostate contours, in particular the apex.

### 7.2.4 Identification of target volumes

CTV1 (first time of treatment) will include prostate and seminal vesicles.

- **Prostate** : The contour includes the entire gland. The definition of the apex is sometimes difficult : frontal and sagittal recontuctions (1 cm above the prostatic bulb) and image fusion with MRI. If doubt, especially if the apical biopsies are positive or if the lesion is situated low on the MRI, additional cuts will be added near the bottom. The principal anticipated toxicity of an irradiation administered too low is alteration of sexual function. The base is identified with the help of vesicular opacification
- **Seminal vesicles:** only the proximal part of the seminal vesicles will be included in the CTV1.

### 7.2.5 Localization of the prostate

If conformal radiotherapy with intensity modulation is used for the first treatment phase, daily repositioning of the prostate on the implants or with the Conebeam CT is requested.

### 7.2.6 Dosimetry

Four to seven beams will be used with energy photons between 6 and 21 MV. PTV1 is defined by 1 cm expansion of CTV1, margin reduced posteriorly to 0.5 cm in order to protect the rectum. Beams limits are defined by additional margin around the PTV. The dimensions of this margin are a function of the penumbra of the beam (ICRU 50).

We will strive to respect ICRU 50 recommendations (doses received at each point of the PTV must be superior to 95% and less than 107% of the prescribed dose). In order to respect the constraints on the dose received by healthy tissues, the minimal dose within the target volume is recognized to be less than the prescribed dose. We will strive to have the minimal dose within the PTV to be at least 95% of the prescribed dose. Dose prescription is made at ICRU point (conformal radiotherapy). If case of IMRT, the mean dose to the PTV1 would be at least equivalent to prescribe dose. In all cases, heterogenity will be considered.

### 7.2.7 Doses to critical organs

#### Contouring organs at risk

**Rectum and anal canal :**

- Lower limit : 2 cm below the CTV1
- Upper limit : at the junction of the first sigmoid loop
- The rectal volume is the volume included between the external contour and an internal contour of 5 mm (“dose-wall histogram: DWH”)

**Bladder :**

- External contouring of the entirety from slices where it is visible. The bladder volume is the volume included between the external contour and an internal contour defined at 7 mm from the former
- When the prostate sticks out into the bladder, it will be necessary to ascertain that there is not an overlap between the critical organs and the CTV.

**Intestine and sigmoid :**

- We will strive to quantify in one or two separate critical volumes the small intestine and the sigmoid

**Penile bulb :**

- Drawn on the cuts where it appears

#### Dose constraints

Summarized in the table below :

| **Rectum** | **Bladder** | **Femoral heads** |
| --- | --- | --- |
| <50 Gy in 5% of the volume | <50 Gy in 5% of the volume | Maximum point <30 Gy |
| <47 Gy in 30% of the volume | - |
| <40 Gy in 40% of the volume | <40 Gy in 50% of the volume |

## 7.3 SECOND PHASE : Hypofractionated stereotactic boost irradiation

**Hypofractionated stereotactic boost irradiation begins in the 10 days following the last session of the first phase.**

The 3 fractions, at 6 Gy each, are delivered over 5 to 9 days (typically Tuesday, Friday and Tuesday). An interval of 48 hours will be observed between two sessions of stereotactic radiotherapy delivered by:

- linear accelerator for patients treated in the following centers: CH-Lyon Sud, Centre GF Leclerc-Dijon, Centre L Bérard-Lyon, Val d’Aurelle-Paul Lamarque-Montpellier, Centre Paul Papin-Angers
- CyberKnife for patients treated in the following centers: Centre O Lambret-Lille, Centre A Lacassagne-Nice, Centre A Vautrin-Nancy

### 7.3.1. By linear accelerator

#### Patient positioning

The patient will be in dorsal decubitus, in a stable position reproducible session after session. Different immobilization systems can be used, including a stereotactic frame with vacuum mattress. The immobilization of the patient must be sufficiently reliable in order to ensure that the Clinical Tumor Volume (CTV2) does not exceed the Planning Tumor Volume (PTV2).

#### Image acquisition

Iin case of different contention or modification in patient setting, new image acquisition for planning purposes will be acquired at the discretion of the clinician according to the same guidelines described for phase 1. MRI may be done if a rectal-balloon is placed.

#### Volume definitions

The prostate without the seminal vesicles will represent the Clinical Target Volume (CTV2). Prostate contouring will be done by a radiation oncologist experienced in the definition of prostatic volumes on scanner and MRI. MRI contours will be fused with the scanner contours in order to better define the prostatic apex.

The PTV2 will be obtained by an expansion of 5 mm around the CTV2 according to Boike and al data [Boike 2007].

The prostatic urethra will be delineated on MRI from the bladder up to 2 cm below the apex of prostate. A 3 mm margin will be defined around the urethra.

The rectum will be delineated with an internal expansion of 5 mm from 2 cm below the prostatic apex (without differentiation rectum / anal canal) up to the recto-sigmoid junction.

The empty bladder will be delineated in its totality with an internal expansion of 7 mm.

The femoral heads will be delineated up to the superior pole of the lesser trochanter.

#### Control of prostate movements

Approximately 30 minutes before the planning scanner and at each treatment session, an enema will be administered in order to evacuate matter and gas. An endo-rectal balloon may be placed to limit movement and ensure a better repositioning of the prostate. In order to avoid the transmission of the respiratory movements to the prostate, the bladder will be empty. Movement control can be done either by radioscopy on intra-prostate implants, or by 4D scano-graphy acquisition. The latter method should be used whenever available. In certain cases prostate movements will be limited and will not require immobilization. If prostate movements are greater than 5 mm, abdominal compression, gating or breath holding will be used to limit movements. If, despite that, prostate movements remain greater than 5 mm, stereotactic boost irradiation cannot be done, and irradiation will be accomplished according to conventional methods.

#### Prostate localization

Intra-prostatic markers will be implanted in the prostate before the first scanner acquisition of phase 1. The choice of markers will be left to the discretion of each participating center (gold seeds,…). These must ensure precise repositioning of the prostate (≤ 2 mm). They will also allow a precise fusion between the MRI and the planning scanner. At each stereotactic irradiation session, a precise repositioning (less or equal to 2 mm) of the prostate will be ensured by Conebeam CT acquisition or by systems like Exact Trac. Between two irradiation beams, additional checks can be done in doubtful cases by the acquisition of orthogonal X-ray, the use of a Snap Verification system, or even a new Conebeam CT. If these checks are frequent, the additional dose received must be subtracted from the planned irradiation dose.

#### Dosimetry

The beams will be produced by a linear accelerator with photon energy between 6 and 21 MV. 10 to 15 coplanar or non-coplanar beams will be necessary with 3D dosimetry and, if necessary, the use of intensity modulation. The number of beams will depend on the size of the prostate. In general, the number of beams increases with the size of the prostate. The standardization of the treatment plan will be done at the beam isocenter (prostate center of gravity). Leaves need to be adjusted so that the 85% isodose covers at least 95% of the PTV. The dose prescription will be done on the 85% isodose. The prescribed dose will be 6Gy per fraction. A heterogeneity correction will be mandatory for dosimetry calculation. The maximum point dose shall not, if possible, exceed 115% of the prescribed dose. Any dose greater than 115% of the prescribed dose shall not be outside of the prostate. This maximal dose shall be outside of the urethra. The dose at the urethra volume + 3 mm shall be, if possible, as close as possible to 6Gy and less than 6.5Gy. If not possible, more beams or intensity modulation can be used to decrease the dose at the urethra+3mm. An interval of 48 hours will be respected between each stereotactic radiotherapy session.

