### 6.8.3 Determination of the number of subjects

The number of patients required for this study was calculated using the single step Fleming method with the following hypotheses :

P0 = 85% (level of patients without any toxicity below which the method would provide no

advantage)

P1 = 95% (level of patients without toxicity expected from the proposed methods)

= 5%

= 10% , i.e. a power of 90%

To meet these conditions, the Fleming formula requires 76 evaluable patients to be included (38 by CyberKnife and 38 by linear accelerator). The study's goal will be considered achieved if, of the 76 evaluable patients, at least 70 present no grade 3-4 toxicity according to the NCI scale.

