#### Dosimetry

Beams will be produced by the CyberKnife (photon energy 6 MV). The number of beams shall be based on the prostate volume. The 85% isodose will cover 95% of the PTV. The prescribed dose will be of 6 Gy per fraction. A heterogeneity correction will be mandatory for dosimetry calculation. The maximum point dose shall not, if possible, exceed 115% of the prescribed dose. Any dose greater than 115% of the prescribed dose shall not be outside of the prostate. This maximal dose shall be outside of the urethra. An interval of 48 hours will be observed between two sessions of stereotactic radiotherapy.

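### The LINAC boost prescription makes the protocol's own 115% maximum-dose target unattainable, and the CyberKnife section does not say which isodose carries the 6 Gy

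*Protocol*

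**What the plan says.** **Linear accelerator (Protocol 7.3.1, Dosimetry).** On normalisation: "The standardization of the treatment plan will be done at the beam isocenter (prostate center of gravity"). On coverage: "Leaves need to be adjusted so that the 85% isodose covers at least 95% of the PTV". On prescription: "The dose prescription will be done on the 85% isodose", and "The prescribed dose will be 6Gy per fraction". On the maximum: "The maximum point dose shall not, if possible, exceed 115% of the prescribed dose". The next sentence limits where higher doses may fall: "Any dose greater than 115% of the prescribed dose shall not be outside of the prostate". The maximum must also avoid the urethra, and the urethra with its 3 mm margin should, where possible, be close to 6 Gy and below 6.5 Gy.

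**CyberKnife (Protocol 7.3.2, Dosimetry).** The section gives the same 6 Gy per fraction, the same 115% target, the same restriction to the prostate and the same rule on the urethra. Its coverage rule is: "The 85% isodose will cover 95% of the PTV". It names no isodose on which the 6 Gy is prescribed, no normalisation point, and no dose figure for the urethra plus 3 mm, although its volume definitions have that structure contoured.

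**Aim (Protocol 4.3.5).** The combined treatment is meant to reach a biologically equivalent dose of about 80 Gy. Sections 4.3.3 and 4.3.5 use an alpha/beta of 3 Gy when they discuss EQD2.

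**The concern.** A percentage isodose has a dose in Gy only once the 100% point and the prescription isodose are both fixed. In 7.3.1 both are fixed, and together they imply a dose at the isocentre that already exceeds the 115% target. A target qualified by possibility still presupposes that some plans can reach it. If none can, it cannot guide planning or help anyone audit a plan.

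In 7.3.2 the prescription isodose and the 100% point are both left open, so the same 3 x 6 Gy label can describe two different boosts. The device is determined by the treating centre (7.3), so a difference in reading would follow device and centre. Delivered dose bears directly on the primary endpoint, urinary and rectal toxicity. Section 6.7.4 describes cumulative dosimetry only as single or dual, so that section does not secure a record of which reading a centre used.

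**Working it through.** **Inputs from the protocol.** Boost of 3 fractions, 6 Gy prescribed per fraction; LINAC prescription isodose 85%; LINAC normalisation at the isocentre; maximum-dose target 115%; LINAC urethra figure 6.5 Gy (all 7.3 to 7.3.2). First phase of 46 Gy in 2 Gy fractions (7.2). Alpha/beta of 3 Gy (4.3.3, 4.3.5).

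**Step 1: the protocol's own aim.** EQD2 = 46 + D x (d + 3)/5, where D is the total boost dose and d the dose per fraction. For 3 x 6 Gy: 46 + 18 x 9/5 = 78.4 Gy. This agrees with the stated aim of about 80 Gy.

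**Step 2: the LINAC conflict.**
- Target: 1.15 x 6 = 6.90 Gy per fraction.
- Isocentre dose when 6 Gy lies on the 85% isodose: 6/0.85 = 7.06 Gy, which is 7.06/6 = 117.6% of the prescribed dose.
- The maximum is at least the isocentre dose, so it is at least 117.6%.
- Excess: 7.06 - 6.90 = 0.16 Gy per fraction, or 2.6 percentage points.
- The 115% target is compatible only with a prescription isodose of at least 1/1.15 = 87.0% of the maximum. This shows the size of the mismatch; it is not a proposal.

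If the 85% were taken relative to a hotter point elsewhere, that point would itself receive 7.06 Gy, so the result does not depend on the isocentre being the maximum.

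**Step 3: the excess in EQD2 at the maximum.**
- At 7.06 Gy per fraction: D = 21.18 Gy; 46 + 21.18 x 10.06/5 = 88.6 Gy.
- At exactly 115%: D = 20.7 Gy; 46 + 20.7 x 9.9/5 = 87.0 Gy.
- Difference: 1.6 Gy.

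**Step 4: the two CyberKnife readings.**

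| Reading of 7.3.2 | Dose per fraction on the 85% isodose | Dose per fraction at 100% | Total EQD2 on the 85% isodose | Total EQD2 at 100% |
|---|---|---|---|---|
| 6 Gy on the 85% isodose | 6.0 Gy | 7.06 Gy | 78.4 Gy | 88.6 Gy |
| 6 Gy at 100% | 0.85 x 6 = 5.1 Gy | 6.0 Gy | 46 + 15.3 x 8.1/5 = 70.8 Gy | 78.4 Gy |

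The first reading reproduces the LINAC conflict. The second forces no conflict with 115%, but leaves the covering isodose at 70.8 Gy against the aim of about 80 Gy.

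**Step 5: the urethra figure.** The LINAC figure of 6.5 Gy is 6.5/6 = 108.3% of the prescribed dose and 6.5/7.06 = 92.1% of the isocentre dose. Section 7.3.2 has no counterpart.

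**The case against.** **The cap is soft.** A reader might infer that 7.3.1 violates a hard limit. It does not. The 115% figure is qualified by possibility, and the following sentence rules out higher doses only outside the prostate. The isocentre is defined as the centre of gravity of the prostate, where the text leaves room for 117.6%. This objection stands and limits the finding to a target that cannot be reached.

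**The excess is small.** Also true: 0.16 Gy per fraction, 1.6 Gy in EQD2 at the maximum. The larger gaps in Step 4 compare two readings of the CyberKnife text and do not measure the LINAC conflict.

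**CyberKnife shares most of the specification.** The 5 mm margin, coverage level, 115% target, restriction to the prostate, rule on the maximum and the urethra, and organ dose tables all match. The aim of about 80 Gy also sits poorly with 70.8 Gy. That makes the second reading less natural but does not exclude it, because 7.3.2 never says what the 6 Gy refers to. What is shown for CyberKnife is ambiguity, not a breach, and the documents do not show that the two groups received different doses.

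**Pooling.** A reader might go further and infer that the single success rule in 6.8.3 is faulty because it combines the devices. The documents do not support that. The primary objective in 5.1 covers delivery by either device. The rule reproduces: the one-sided Fleming formula gives 75.1, rounded up to 76, with a cut-off of 70, exact alpha 0.0497 and power 0.914. A pooled rule can mask a difference between devices, but its size rests on rates the protocol does not give by device. With assumed toxicity of 15% on one device and 5% on the other, the rule passes with probability 35%; at 15% and 1%, 59%. Adding a limit of 5 events among 38 per device would only lower these to 32.6% and 47%. Adding a per-device criterion is a design preference, not the correction of an error.

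**Conclusion.** The point holds for the dosimetry text and should be fixed. In 7.3.1, normalisation at the isocentre with 6 Gy on the 85% isodose forces at least 117.6% of the prescribed dose, so the 115% target can never be met. In 7.3.2, the missing prescription isodose and normalisation point leave either 6 or 5.1 Gy per fraction on the covering isodose, a difference of 78.4 - 70.8 = 7.6 Gy in total EQD2.

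The LINAC result assumes only that isodose percentages refer to 100% at the isocentre or at a hotter point. The EQD2 figures assume an alpha/beta of 3 Gy and the full 46 Gy at the point considered; the protocol uses that alpha/beta elsewhere but does not tie it to the 80 Gy aim. The difference in physical dose needs neither assumption. Nothing here bears on the correctness of the 76-patient, 70-success rule.

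**What to change.** The sponsor's physicists and clinicians should reconcile the normalisation point, the prescription isodose, the 115% target and the urethra passages, first within 7.3.1 and then between 7.3.1 and 7.3.2. They should state one prescription convention that applies to both devices. If the urethra figure is meant to differ by device, the text should say so. Which isodose, dose or limit is right is for them to decide, and none is proposed here.

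The cost is an amendment to the two Dosimetry subsections and its communication to the centres. Sample size, decision rule and power stay as they are, and 6.8.3 needs no change on this account.

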**Dose constraints**

| **Rectum** | **Bladder** | **Femoral heads** |
| --- | --- | --- |
| <75% of the prescribed dose in 20% of the volume | <75% of the prescribed dose in 20% of the volume | Maximum point <40 % of the prescribed dose |
| V65 < 30% | <55% of the prescribed dose in 35% of the volume with a maximum prescribed dose at 5% of the organ |
| <55% of the prescribed dose in 35% of the volume with a maximum prescribed dose at 5% of the organ |

### 7.3.2 By CyberKnife

#### Patient positioning

The patient will be in dorsal decubitus, in a stable position reproducible session after session. Patient immobilization must be sufficiently reliable in order to ensure that the Clinical Tumor Volume (CTV2) remains within the Planning Tumor Volume (PTV2).

#### Image acquisition

New image acquisition for planning purposes could be acquired at the discretion of the clinician according to the same guidelines described for phase 1.

#### Volume definitions

The prostate without the seminal vesicles will represent the Clinical Target Volume (CTV2). Prostate contouring will be done by a radiation oncologist experienced in the definition of prostatic volumes on scanner and MRI. MRI contours will be fused with the scanner contours in order to better define the prostatic apex.

The PTV2 will be obtained by an expansion of 5 mm around the CTV2.

The prostatic urethra will be delineated on MRI from the bladder up to 2 cm below the apex of prostate. A 3 mm margin will be defined around the urethra.

The rectum will be delineated with an internal expansion of 5 mm from 2 cm below the prostatic apex (without differentiation rectum / anal canal) up to the recto-sigmoid junction.

The empty bladder will be delineated in its totality with an internal expansion of 7 mm.

The femoral heads will be delineated up to the superior pole of the lesser trochanter

#### Control of prostate movements

The treatment is done using with CyberKnife “synchrony” module, to track the tumor lesion with the fiducials previously implanted. If tracking is not possible, the patient will be withdrawn from the study.

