| **ASSESSMENT CRITERIA** | Primary  Urinary or rectal toxicity: According to the NCI-CTCAE v3.0 rating scale (appendix 10). Acute toxicities are defined as all toxicities occurring in the 6 months following the start of radiotherapy. Late toxicities are defined as all toxicities occurring beyond 6 months.  **Secondary**   - Rate of local control at 3 years: non progression of : - PSA level according to the Phoenix definition (nadir to be obtained) - Clinical examination (rectal touch) - No pathological signal on MRI - Median time without progression for the entire cohort: interval between the date of inclusion and the date of progression, whether clinical (rectal touch) or radiological (prostatic MRI). - Median overall survival: Median time for the entire cohort comprising the time between the date of inclusion and the date of death, whatever the cause. - Survival without biological failure at 3 years: Phoenix criteria for PSA increase (nadir + 2 ng/ml) (see chapter 6.7.3) - Technical criteria: Implantation of markers, treatment time, cumulative dosimetry, administration and length of boost session - PSA kinetics during the entire treatment (between the two irradiation phases) and after treatment - Sexual dysfunction = international questionnaire IIEF 5 - Urinary discomfort = IPSS questionnaire |
| **STATISTICAL ANALYSIS** | The initial characteristics of included patients will be presented in the form of summary tables. Continuous variables will be summarized by conventional descriptive statistics parameters (median and outlying  values, mean and standard deviation when necessary). Category variables will be presented in the form of contingency tables (absolute frequency and percentage of each modality), additionally stating the number of missing data, along with the 95% confidence interval.  Subject inclusion and exclusion criteria will be checked against data entered into the case report forms when possible. Any deviations from the protocol will be documented.  Survival will be analyzed by the Kaplan-Meier nonparametric method. |

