## 6.4 Early study withdrawal criteria

The length of patient participation in the study is at least 3 months after the last radiotherapy session.

The conditions for early termination of the study are :

- Failure to track the tumor
- Failure to place fiducial markers
- Dose-volume histograms (DVH) constraints not achievable
- Interval greater than 3 weeks between the end of the radiation therapy phase and the first session of hypofractionated stereotactic boost irradiation

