### 6.6.4 Follow-up visit

Evaluation will be done 6, 9, 12, 18, 24 and 30 months after the last radiotherapy session :

 Clinical examination

- Weight, performance status or ECOG (appendix 3)
- Digital rectal exam
- Evaluation of late toxicity associated with irradiation

 Blood tests

- Tumor marker: PSA

 Paraclinic examinations

- Prostate and pelvis MRI (at 6, 12 and 24 month)

 Questionnaires

- Sexual quality of life “IIEF-5” (appendix 11)

- Urinary discomfort “IPSS” (appendix 12)

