## 6.7 Assessment Criteria

### 6.7.1 Tolerance evaluation

Acute tolerance ( 6 months from the end of radiotherapy) and late effects associated with radiotherapy (> 6 months, from the end of radiotherapy) will be assessed according to the NCI-CTCAE scale, version 3.0 (appendix 10), from the data collected by the clinician.

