#### Localization of the prostate

Intra-prostatic markers will be implanted in the prostate before the first scanner acquisition of phase 1. The choice of markers will be left to the discretion of each participating center (gold seeds,…). They must ensure precise repositioning of the prostate (≤ 2 mm). They will also allow a precise fusion between the MRI and the planning scanner. At each stereotactic irradiation session, a precise repositioning (less or equal to 2 mm) of the prostate will be ensured.

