**2nd phase**

**Stereotactic boost irradiation: 3 x 6 Gy**

Over 5 to 9 days(1)

CyberKnife or Linear Accelerator (see chapter 7.3)

D-21 D1 to D5 D8 to D12 D15 to D19 D22 to D26 D29 to 31 F 1 2 3

Start within 10 days of the last session of the 1st phase

*Interval between fiducials placement and the planning CT-scan is 7 days*

Follow-up after the last stereotactic irradiation session : at 3, 6, 9 and 12 months

at 18, 24, 30 and 36 months (end of study)

then at 48 and 60 months

**in case of technical problem, the authorized postponement is 15 days*

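### Tracking failure withdraws a CyberKnife patient from the study, not only from the boost, with no limit to the time before fraction 1; a partly boosted man would have no scheduled late-toxicity grading

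*Protocol*

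**What the plan says.** **Exit rule.** Section 7.3.2, on control of prostate movements with the CyberKnife: "If tracking is not possible, the patient will be withdrawn from the study". Section 6.4 includes "Failure to track the tumor" in its list of conditions for early termination. Neither statement has a timing limit, and neither provides for follow-up after exit.

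**Positioning.** The localization paragraph of 7.3.2 states: "At each stereotactic irradiation session, a precise repositioning (less or equal to 2 mm) of the prostate will be ensured". The boost is three fractions of 6 Gy over 5 to 9 days (7.3).

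**Minimum participation.** Section 6.4: "The length of patient participation in the study is at least 3 months after the last radiotherapy session".

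**Late toxicity.** The synopsis makes urinary or rectal toxicity the primary criterion and, counting from the start of radiotherapy, says: "Late toxicities are defined as all toxicities occurring beyond 6 months". Section 6.7.1 counts from the end of treatment: "late effects associated with radiotherapy (> 6 months, from the end of radiotherapy".

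**Visits.** Section 6.6.3 sets a 3-month visit for acute toxicity. Section 6.6.4 then says: "Evaluation will be done 6, 9, 12, 18, 24 and 30 months after the last radiotherapy session", with late toxicity assessed at each. Section 6.6.5 adds month 36, and 6.6.6 adds months 48 and 60.

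**Technical problems.** A note to Appendix 1 reads: "in case of technical problem, the authorized postponement is 15 days".

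**The concern.** Being unable to continue the boost is a reason to stop the boost. It is not a reason to stop observing a man who has already received part of it. With one or two 6 Gy fractions delivered on top of 46 Gy, he carries some of the risk that the trial exists to measure. The rule as worded ends his participation, and nothing in the text exempts him from it.

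What is at stake is late safety information on exposed patients and, if such a man is counted among the 76 evaluable patients, his late status for the primary criterion. Section 6.7.2 makes a patient assessable after one boost session. It says so under tumor efficacy, so whether the same rule governs the toxicity count is not stated.

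**Working it through.** **1. The plan's own figure.** Section 6.8.3 gives p0 = 0.85, p1 = 0.95, alpha 5%, power 90%, N = 76, and success if at least 70 patients have no grade 3-4 toxicity. Sidedness is not stated; a one-sided test reproduces N:

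n = [(1.645 × √(0.85 × 0.15) + 1.282 × √(0.95 × 0.05)) / 0.10]² = 75.1, rounded up to 76.

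Exact binomial: P(X ≥ 70 | 76, 0.85) = 0.0497 and P(X ≥ 70 | 76, 0.95) = 0.914. The design holds, and the point below does not touch it.

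**2. Can the rule apply after fraction 1?** CyberKnife treatment is carried out by tracking the implanted markers, and precise repositioning is required at every session. Tracking is therefore needed for fractions 2 and 3 as well as fraction 1. With no timing limit in 6.4 or 7.3.2, the words cover a failure after 6 Gy or 12 Gy of boost.

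**3. Scheduled late visits lost.**

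| Section | Visits more than 6 months after the end of radiotherapy | Count |
|---|---|---|
| 6.6.4 | 9, 12, 18, 24, 30 months | 5 |
| 6.6.5 | 36 months | 1 |
| 6.6.6 | 48, 60 months | 2 |
| Total | | 8 |

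This is the count under 6.7.1. The synopsis counts from the start of radiotherapy. Phase 1 alone takes at least 31 days, so the 6-month visit falls no earlier than about 31 + 182.6 = 213.6 days after the start, well past 6 months (182.6 days). The count is then 8 + 1 = 9. A man withdrawn during the boost keeps none of them.

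**4. Does another provision restore late grading?**

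- *Minimum participation (6.4):* 3 months after the last session is short of the 6 months in 6.7.1, and the visit at that time is the acute one.
- *Evaluation at premature end (6.6.5):* it refers to 6.5, which lists progression, the patient's decision, the investigator's decision and death, but not tracking failure. If applied anyway, it would take place at exit, before the late period.
- *Postponement (Appendix 1):* it allows 15 days for a technical problem but does not say what follows if tracking is still impossible.
- *Adverse event reporting (6.7.1):* related late serious adverse events are declared without time limit, and serious events are followed to resolution even after exit. This covers a good part of what matters, but it depends on an event being serious and reaching the investigator.

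**5. What the reporting route can miss.** The success rule counts grade 3-4 toxicity, whether serious or not. In Appendix 10, voiding at least hourly is grade 3 urinary frequency, and rectal bleeding that needs endoscopic treatment is grade 3. Neither is automatically serious under 6.7.1, where a hospital stay under 24 hours does not qualify. Such an event could go unrecorded once scheduled visits have stopped.

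**The case against.** The best defence is context. The other three conditions in 6.4 (failed marker placement, unattainable dose-volume constraints, too long an interval before the first boost session) are all settled before the boost. The phrase in 7.3.2 also reads like a feasibility test. The authors probably had in mind a man who never starts the boost. This stands as a view of intent, and it is why affected men may be few or none. It does not supply the missing limit.

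Exit wording is also loose elsewhere. Section 6.5 requires termination on progression, while 7.5 keeps a man with distant progression in the study and under follow-up. Three months is a floor, not a ceiling. A sensible investigator might therefore go on seeing the patient. That is true, but where the protocol wants follow-up to continue it says so, and for tracking failure it does not.

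Safety capture is wider than a bare reading of the exit rule implies. Rectitis and cystitis are named as expected serious events, and the medically significant category leaves room for judgement. This narrows the loss to the events in step 5.

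Three stronger readings are tempting, and the documents support none of them:

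- *The error rates of the primary test are distorted.* That would need an assumed number of men and an assumed rule for scoring unknown late status. The protocol gives neither, and scoring may be set in a statistical analysis plan that is not shown.
- *The 3-month minimum misses the late period under both definitions.* Under the synopsis this rests on a thin margin. The slowest permitted course ends on day 42 + 21 + 9 + 15 = 87. Adding 91.3 days gives day 178.3, only 4.3 days short of 182.6. Conventional fractions given after a stopped boost could erase that margin.
- *Linear accelerator patients are treated differently.* For motion above 5 mm, 7.3.1 replaces the boost with conventional irradiation and does not mention study status. Handling there is unspecified, not shown to differ.

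**Conclusion.** The point holds, and it is minor. Sections 6.4 and 7.3.2, followed literally, end study participation for a man whose tracking fails after one or two boost fractions. They leave him 0 of 8 scheduled late-toxicity visits (0 of 9 with the 6-month visit). The practical loss is mainly non-serious grade 3 urinary or rectal events and events not brought to the investigator.

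The conclusion rests on the literal wording and on tracking being able to fail between fractions. How often that happens is not given, and it may be never. No stated number is wrong: N = 76 and the cutoff of 70 stand.

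**What to change.** Amend 6.4 and 7.3.2 to say that tracking failure after at least one boost fraction stops the boost but not study participation, and that the patient stays in the toxicity visits of 6.6.3 to 6.6.6. The treatment given in place of the remaining fractions stays a clinical decision.

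The cost is a wording change in two sections and, if any such patient occurs, a few routine follow-up visits that the protocol already describes. Sample size and decision rule stay as they are.
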